**Sampling, including sample size and statistical power**

Participants will be sampled from the database of patients already receiving care at the project clinics. Information about gender, whether on ART, and last clinic visit will be used to create a list of potential participants. From that list, patients will be randomly selected to create a list of patients to approach about participating in the project. When patients arrive at the clinic the list will be checked and if their name is on it they will be asked if they are interested in participating in the project (see enrollment section below for further description). If they are not, their name will be removed from the list. Each clinic will enroll approximately half of each gender and half who are on ART. A tally of persons in each of the gender by ART cells will be kept updated daily. As each of the cells near the enrollment targets the study coordinator will monitor the potential participant list to ensure that appropriate numbers of participants are in each group.

The primary outcome variable for the project will be participant self-report of any unprotected sex in the past 3 months. Prior studies have found rates of condom use to be very low in the areas in which this project will be conducted (Arthur et al., 2007; Feldblum et al., 2000; Kapiga et al., 2006; Mwaluko et al., 2003; Norman, 2003; Stanton et al., 1999; Ross et al., 2007; Watson-Jones et al., 2007). We will assume a rate of at least 50% for any unprotected sex in the past 3 months in the comparison condition for sample size estimation.

Although the proposed project includes measurements at three time points (baseline, 6 months and 12 months), sample size estimates are presented for the simple difference between proportions in the two project conditions at the 12-month follow-up only. This approach is conservative because analytic approaches taking into account the multiple observations on each participant will be more powerful. We use the cross-sectional approach for sample size estimation because no prior data are available on which to base prediction of the pattern of intervention effects over time and the magnitude of the over-time correlation of groups and group members that we can expect in this project. Our sample size estimates do take into account expectations of attrition in the project cohort, which we expect to be moderate (at most 30% at the 12-month follow-up).

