In the following sample size table, we present calculations for the number of clinics needed for at least 80% power to detect differences of varying size between the intervention and comparison conditions with a two-sided test and α=0.05. Sample size estimates are based on a formula in Murray (1998) for group-randomized trials:

Where g is the number of groups per condition, and are the event rates in the two project conditions, *m* is the number of members per group (clinic), is the intraclass correlation coefficient measuring the correlation of members nested within groups, nested within project conditions, and and are critical values from the t-distribution.

Table 1 presents the sample sizes necessary for at least 80% power to detect a 20-30% reduction in the rate of unprotected sex in the past 3 months in the treatment condition compared to the comparison condition at the 12-month follow-up. We use 50% as the rate of unprotected sex in the comparison condition for sample size estimation; if the actual rate is higher or lower with the same reduction in the treatment condition, power will be greater, as variance in the binomial distribution is largest at 50% and decreases as the event rate moves away from 50% in either direction. Power calculations for group-randomized trials also need to take the expected intraclass correlation coefficient (ICC) into account to have adequate power. However, there are no prior published reports of ICCs for sexual risk behaviors among clinic attendees in sub-Saharan Africa on which to base our power calculations. A prior study did report an ICC of .0011 for STI prevalence at the community level in Kenya (Feldblum et al., 2000), and another study presented an ICC of about .01 for any unprotected sex in the past 90 days in a neighborhood-randomized trial in the U.S. (Pals et al., 2008). ICCs are generally larger for behavioral variables than for biologic variables and also generally increase as the group size decreases (e.g. larger for clinics than for communities). Murray and Blitstein (2003) showed that including multiple timepoints in analytic models can substantially reduce the ICC. Based on these prior results, we use ICCs of .01 and .02 for sample size estimation.

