**Table 1. Number of groups and members per condition needed for at least 80% power to detect a 20-30% difference between intervention and comparison conditions in report of any unprotected sex in the past 3 months (assuming intraclass correlations of 0.01 or 0.02).**

| **P1** | **P2** | | **ICC** | **Absolute Difference** | **% Difference** | **Members per group enrolled** | **Members per group retained** | **Number of groups needed per condition** |
| --- | --- | --- | --- | --- | --- | --- | --- | --- |
| .50 | .3875 | | .01 | .1125 | 22.5 | 200 | 140 | 7 |
| .50 | .3750 | | .01 | .1250 | 25 | 200 | 140 | 6 |
| .50 | .3625 | | .01 | .1375 | 27.5 | 200 | 140 | 5 |
| .50 | .3500 | | .01 | .1500 | 30 | 200 | 140 | 4 |
| .50 | | .3750 | .02 | .1250 | 25 | 200 | 140 | 9 |
| .50 | | .3625 | .02 | .1375 | 27.5 | 200 | 140 | 7 |
| .50 | | .3500 | .02 | .1500 | 30 | 200 | 140 | 6 |

P1=proportion reporting any unprotected sex in the comparison group; P2=proportion reporting any unprotected sex in the intervention group

Table 1 shows that with 9 clinics per condition, each with 200 patients enrolled, the project would have at least 80% power to detect a 25% difference between intervention and comparison (absolute difference of 12.5%) with an ICC of 0.02. If the ICC is smaller or the intervention effect larger, power will be greater then 80%.

Summary

We anticipate enrolling 200 patients per clinic with 9 clinics per condition (3 per condition per country), for a total of 18 clinics and approximately 3600 patients (at least 2520 retained at 12 months). Power calculations demonstrate that this number of participants will allow us at least 80% power to detect a 25% relative difference between conditions for the primary outcome variable of any unprotected sex during the past 3 months, allowing for up to 30% loss to follow-up.

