**PROCEDURES/METHODS: DATA HANDLING AND ANALYSIS**

**Data analysis plan**

The proposed project will be a multi-site nested cohort group-randomized trial (GRT) with a-priori matching at the clinic level. Here, group refers to clinic, and “study condition” or “condition” will refer to intervention vs. control assignment. Matching of clinics will be performed in the design of the project to improve balance across study conditions on factors potentially related to the outcome variables. However, the matching will not be reflected in the analysis, as studies have shown that doing so often reduces power in smaller GRTs due to the loss of degrees of freedom (Diehr et al., 1995). Site (country) will be reflected in the analysis, both as an interaction with intervention effect to test for a differential intervention effect by site, and as a main effect to adjust for pre-intervention differences in the outcome variables of interest. If interactions between site and the intervention effect are statistically significant, we will explore intervention effects within country. However, power will be low for this test as the sample sizes within countries are small.

This project presents a number of challenges that must be addressed in the primary and secondary analyses. First, the analytic approach must take into account the correlation among patients within clinics and multiple measurements on the same participants within the same groups over the course of the project. Second, as with any longitudinal cohort study, there is potential for attrition over the course of the study and differential attrition between intervention and comparison conditions. Finally, many of the outcome measures used to assess the impact of the intervention will be non-normally distributed, including dichotomous indicators for whether risky sexual behaviors occurred and frequency variables indicating how many partners a participant reported.

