For the main outcome analysis, numerous options are available for the test of the effectiveness of the intervention. Mixed-model regression methods are often used for the analysis of GRTs and easily accommodate the over-time correlation at the group and member level, as well as the correlation of observations within groups. Using different procedures within SAS, such as PROC MIXED, PROC GLIMMIX, and PROC NLMIXED, mixed-model regression can be performed for many common statistical distributions, and some less-common ones often used in HIV research (e.g., censored log-normal for viral load measurements). We propose to use mixed-model regression methods to test for a difference between study conditions at 6 and 12 months, incorporating the baseline measurement as a covariate. Initial models will include fixed effects for the baseline value of the outcome variable, country, study condition, time (6 or 12 month measurement), the country by study condition interaction, the time by study condition interaction, the time by country interaction and the three-way interaction between time, study condition and country. Models will also include random effects for group and group by time. If the country by time by condition interaction is significant, the time by condition interaction will be tested stratified by country to determine the pattern of intervention effects for each country separately. Because power is based on the number of clinics, however, tests for country differences will have low power relative to the overall test for an intervention effect. If the three-way interaction is not significant, it will be dropped from the model and further evaluation of intervention effects will focus on the time by condition term. If this term is significant, condition effects will be evaluated stratified by timepoint; if it is not significant, a pooled estimate of the intervention effects (across timepoints) will be computed. This effect estimate has the advantage of greater power than a test at either timepoint alone, due to the larger number of observations. The random effects for group and time by group will control for the correlation within participant over time in these models. Also, the country by condition effect will be tested to determine whether the study condition effect (pooled across time) differs by country.

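### The outcome model has no participant term, yet the protocol says its clinic-level random effects control within-participant correlation; the test that decides whether to pool visits can be conservative as a result

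*Protocol*

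**What the plan says.** The Data analysis plan defines group as clinic. It says the analysis must allow for correlation among patients of a clinic and for "multiple measurements on the same participants within the same groups over the course of the project". It notes that mixed models can accommodate over-time correlation at both group and member level.

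The chosen model is a mixed regression to "test for a difference between study conditions at 6 and 12 months, incorporating the baseline measurement as a covariate", so each participant can contribute two outcome rows. On random effects it says: "Models will also include random effects for group and group by time". No participant effect or within-participant covariance is listed. It then asserts: "The random effects for group and time by group will control for the correlation within participant over time in these models".

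The time-by-condition term determines what is reported. "If this term is significant, condition effects will be evaluated stratified by timepoint; if it is not significant, a pooled estimate" across visits is computed instead. After the observed-data analysis, the same section repeats the primary outcome analysis with multiple imputation.

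**The concern.** A clinic effect and a clinic-by-time effect take the same value for every patient of that clinic, or of that clinic at that visit. Under the stated model, two answers from one patient are no more correlated than answers from two different patients of the same clinic. The baseline covariate removes part of the within-person correlation between 6 and 12 months, but not all of it. The quoted assertion is therefore wrong, and the model does not meet the section's own requirement.

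Two things are at stake. First, a test of change between visits should benefit from comparing each person with himself or herself. Without a participant term its standard error can be too large, which steers the analysis towards pooling when the effect wanes or is delayed. Second, up to 30% loss is expected at 12 months. A model without a participant term cannot use a person's 6-month answer when the 12-month answer is missing.

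**Working it through.** **The protocol's own figure first.** Inputs from the sample size section: 0.50 v 0.375, ICC 0.02, 140 retained per clinic, 9 clinics per condition, two-sided α = 0.05.

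- Variance of the difference = (0.25 + 0.2344) × (1 + 139 × 0.02) / (140 × 9) = 0.00145, so SE = 0.0381.
- 0.125 / 0.0381 = 3.28. With t = 2.12 on 16 df, power is 86.8%. The formula needs 7.6, so 8, clinics.

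The claim of "at least 80% power to detect a 25% difference between intervention and comparison (absolute difference of 12.5%) with an ICC of 0.02" therefore holds with 9 clinics. It rests on a cross-sectional 12-month comparison, so within-person correlation does not enter it.

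**Time-by-condition test.** Balanced linear approximation. Let G be the clinic-by-time variance, M the participant variance and E the residual, as shares of within-clinic variance with M + E = 1. The residual within-person correlation after baseline adjustment is ρ = M. The protocol gives no value, so 0.2 to 0.5 is assumed. There are 12 df (18 clinics less 6 country-by-condition cells). The binomial variance is (0.25 + 0.2344)/2 = 0.242.

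- True variance of the interaction contrast: (2/9) × 2 × (G + E/m) × 0.242.
- The clinic-by-time mean square has expectation mG + E, but the planned residual estimates M + E.
- When G < M/m (0.2/140 = 0.0014 to 0.5/140 = 0.0036), the clinic-by-time variance tends to be estimated at zero. The standard error is then inflated by 1/√(1 − ρ): 1.12 at ρ = 0.2, 1.41 at ρ = 0.5.

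By hand, at G = 0 and ρ = 0.5:

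- True SE = √(0.444 × 0.121/140) = 0.0196. Planned SE = √(0.444 × 0.242/140) = 0.0277.
- The planned test rejects beyond 2.179 × 0.0277 = 0.0604.
- Type I error = P(|Z| > 0.0604/0.0196 = 3.08) ≈ 0.2%.
- Power for a 6-point change in effect = P(Z > (0.0604 − 0.06)/0.0196) ≈ 49%.

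Simulation, with variance components truncated at zero:

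| Clinic-by-time variance | ρ | Type I error, planned | Type I error, with participant term |
|---|---|---|---|
| 0 | 0.2 | 1.3% | 2.2% |
| 0 | 0.23–0.33 | 0.7–1.2% | 2.2% |
| 0 | 0.5 | 0.2% | 2.2% |
| 0.5% of total | 0.2–0.33 | 3.6–3.9% | 4.4–4.7% |
| 1% of total (half of an ICC of 0.02) | 0.2–0.6 | 4.5–4.8% | 4.9–5.0% |

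At zero clinic-by-time variance, power for the 6-point change is about 47–49% as planned, against about 54% (ρ = 0.2) to 76% (ρ = 0.5) with the term. The 2.2% shows that the zero boundary leaves some conservatism even after the repair.

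A smaller logistic simulation (400 trials per setting, country terms omitted, 16 df) agrees in direction. With conditional correlation 0.23–0.32 and 10% of the ICC as clinic-by-time, type I error is 1.8–2.5%. With 50% of an ICC of 0.02 and correlation 0.23 it is 4.5%. Monte Carlo error is about 1.1 points.

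**Pooled condition test.** The clinic variance estimate absorbs M/m. Type I error under the planned model is 4.5–5.0% (linear approximation).

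**Missing 12-month answers.** All dropout patterns here are assumed, with no true effect.

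- Rate 40% in both arms, correlation 0.5, retention 60% v 80% by 6-month yes/no in one arm and 70% throughout in the other. Unadjusted, the first arm shows (0.4 × 0.6 × 0.7 + 0.6 × 0.8 × 0.2)/(0.24 + 0.48) = 0.367 against 0.40, a bias of 3.3 points. With the planned baseline covariate it is 1.7 points. At correlation 0.3 the figures are 2.0 and 1.4.
- 30% loss per arm, dropout depending on the 6-month answer in opposite directions by arm. With baseline in the model the bias is 1.4–1.8 points (25% v 35% dropout) or 2.9–3.6 points (20% v 40%). It is about 0 once the 6-month answer is used.

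**The case against.** Several points on the other side stand.

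- A reader might infer that the main effectiveness test is invalid or has inflated false-positive risk. It does not: the pooled test keeps close to 5%, and the sample size is untouched. The affected test is an interaction test that errs conservatively and for which the protocol claims no power.
- A reader might infer that the plan as a whole ignores 6-month answers when 12-month answers are missing. The planned multiple-imputation repeat draws on associations in the dataset and can use them. The gap lies in the main observed-data analysis.
- A 40% inflation of the standard error is tempting as the headline. It needs residual correlation near 0.5 and no clinic-by-time variance. If 0.3–0.5 are raw exchangeable correlations, adjusting for baseline leaves r/(1 + r) = 0.23–0.33, and the inflation is 14–22%.
- Changes over time would not disappear from view, because the sample Tables 3 and 4 show results separately at 6 and 12 months.
- The section mentions member-level correlation, so the omission may be a drafting slip.

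The last point does not remove the concern. The section goes on to list the random effects and to state that those effects do the job. A programmer following it would fit a model without a participant term.

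**Conclusion.** The statement that clinic and clinic-by-time effects control within-participant correlation is wrong and conflicts with the requirement set in the same section. The practical harm is limited. The test that chooses between visit-specific and pooled effects is conservative when clinic-by-time variance is small and nearly correct when that variance is about 1% of the total. In the main observed-data analysis, 6-month answers cannot inform missing 12-month answers.

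The sizes rest on a balanced linear approximation to a binary outcome and on assumed values for within-person correlation and clinic-by-time variance. Any attrition bias also rests on an assumed dropout pattern, and should be computed with the baseline covariate in the model. This should be corrected before outcome data are analysed, but it does not threaten the pooled test or the sample size.

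**What to change.** 1. Add a participant-level term for the two follow-up visits: either a random intercept for participant within clinic, or a within-participant residual (R-side) covariance across 6 and 12 months.
2. Delete or correct the sentence claiming that the clinic-level effects handle within-participant correlation.
3. State that the imputation model includes the 6-month outcome.

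The design and sample size do not change, and the coding is minor. The real cost is a choice that the plan must state. For a binary outcome, a participant random intercept makes the odds ratio participant-specific. The R-side option keeps the interpretation closer to the planned model, but it is fitted by pseudo-likelihood, so it is not a full-likelihood answer to missing data. Neither option removes the remaining conservatism from the zero-variance boundary.

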**Data collection**

Pilot study

Prior to implementing the project a pilot study will be conducted with approximately 20 clinic patients in each country. The purpose of this pilot will be to determine the length of time to complete the patient questionnaire and determine whether there are items or procedures that need to be improved prior to full project implementation. Participants will be recruited from patients who come into the clinic during the week of the pilot study. A single clinic in each country will serve as the pilot study site. These clinics will be different sites than the intervention and comparison clinics in order to maintain the eligible sample of participants attending the study clinics. The pilot study sites are Katatura Hospital (Namibia), Ocean Road Cancer Institute (Tanzania), Gatundu District Hospital (Kenya).

Potential participants will resemble the project participants as much as possible with regard to gender, length of time attending clinic, and whether they are on ARVs. An interviewer will read potential participants a consent form (Appendix A), ask if they have any questions, and ask them to sign the consent. The interviewer will then proceed with administering the questionnaire. After each section the interviewer will ask the participant some questions (Appendix B) related to the length of the section and whether items were confusing (and if so, which items). Participants will then be thanked for their time and offered a soda or other drink. No additional reimbursement will be provided, as is the custom in the participating countries. Data from the pilot study will be used to inform any needed revisions to the procedures or measures. Once that information has been used to inform the main study, the pilot data will be destroyed. No pilot data will be used in the main study analysis.

Contact information

The contact information form will be collected immediately after the participant completes the consent form to participate in the study. This form will include information on how to best contact the participant, including where they stay, phone numbers, and what is the appropriate mechanism to get in touch with them in order to respect the confidentiality of their study participation. This form will remain in their file and the contact information will be updated during the 6-month follow-up interview.

Patient Questionnaire

All clinic patient study participants will complete an interviewer-administered questionnaire at 3 time points: baseline (enrollment), 6-month, and 12-month follow up (see Figure 2 below for Study flow diagram for clinic patients). All interviews will take place at the HIV clinics after the participants’ regularly scheduled clinic visit whenever possible. All interviews will take place in a private area of the HIV clinic, and the interview will last approximately one hour. Each participant will be individually interviewed by the project interviewer, who will be part of the research team and not a staff member of the clinic. Upon completion, the participant will be offered a soda or other drink and reimbursed for transportation costs to the clinic. No additional reimbursement will be provided, as is the custom in the participating countries. Participants will be encouraged to attend all regular clinic visits as scheduled by their health care provider over the course of the project.

Participants will be asked to provide contact information (see Appendix G) during the baseline interview. They will be asked the best method for contacting them (e.g., text message, phone call, in-person visit, mail/post) for follow-up visit reminders. Approximately one week before their 6- and 12 month follow-up visits, participants will be reminded of their appointments via their preferred method of being contacted. As much as possible the 6- and 12-month visits will be coordinated with regular clinic visits.

Project enrollment will occur over of a 2-3 month period at both intervention and comparison clinics. Following completion of the baseline data collection, the intervention will be implemented at the intervention clinics. Because of the baseline data collection period, the 6-month follow-up will be scheduled for a time estimated to be 6-months after the intervention is integrated into the clinic, so that all intervention clinic participants will have an opportunity to be exposed to the intervention following staff training and implementation. To make the intervention and comparison clinic project procedures as similar as possible, the intervention and comparison clinic 6-month follow-up interviews will occur during the same time period. The same battery of questionnaires will be administered to participants at the 6- and 12-month follow-up interviews, with the exception of some of the sociodemographic questions and items asking about whether something had “ever” happened. At each follow up interview, participants will be offered a soda or other drink and reimbursed for travel costs to the clinic upon completion of the interviews.

